## **2.3 Randomization method**

Participants will be randomly assigned to the AA group and the SAA group in a 1:1 ratio. To minimize selection bias, an independent statistician will use SPSS 28.0 (IBM, Chicago, IL, license code: f56b44b8d8e3562ad8a2) to generate random numbers. These numbers will be enclosed in opaque envelopes. Participants will choose one of these envelopes after agreeing to the principle of random allocation, which will determine their group assignment and the corresponding intervention method.

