#### 3.1.2 Inclusion criteria

1. Meet the diagnostic criteria for ALS;

2. Unilateral low back pain, age 18-60 years;
3. Duration of the disease  $\leq 3$  days;
4. Moderate to severe pain, with the visual analogue score (VAS) between 4 and 8;
5. Signed the informed consent form.

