**Fig 2. Auricular needle and Sham auricular needle**

### **4.3 Procedures**

(1) Auricular acupuncture group: Participants will be in a seated position. The acupuncturist will sterilize the skin of the healthy side AH9 with a 70% alcohol swab. Subsequently, a disposable auricular needle will be pierced vertically into the healthy side AH9. After needle insertion, moderate pressure will be applied to elicit the "de qi" sensation. Upon achieving "de qi", participants will be asked to stand. The acupuncturist will stand behind the participant and support the participant's waist. Then, the participant will be guided through moderate exercises, including forward bending, backward stretching, lateral bending, and rotation, all performed within the limits of their pain tolerance. The range and speed of these movements will gradually increase as the pain decreases.

(2) Sham auricular acupuncture group: This group will receive treatment with a placebo needle of the same shape which lacks a needle body and does not penetrate the skin but is merely taped at the acupoint. The treatment operation is the same as the AA group.

Participants in both groups will receive a single treatment session, with a 10-minute auricular needle retention time.

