#### **4.5 Observation period**

Baseline assessments will be performed before enrollment, and pain intensity and ROM evaluations will be conducted 2, 5, and 10 minutes post-treatment.

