## **5.4 Measurement indicators**

### **5.4.1 Primary outcome**

The primary outcome will be the change in pain intensity from baseline to 10 minutes after treatment as measured using VAS scores.

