- (10) If necessary (e.g., if the participant and their legal representative are illiterate), a witness should be present throughout the informed consent process. After a detailed explanation of the informed consent document, the witness should sign and date the form to confirm that the verbal consent matches the written consent.
- (11) The signing of the informed consent should occur before any research procedure

is performed. If the consent cannot be signed before the study due to justifiable reasons, it should be signed as soon as possible, and the form should note the date and explanation for any amendments.

(12) Two copies of the signed and dated informed consent form should be made; one copy is given to the participant or their legal representative, and the other is kept by the researchers for archiving.

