## **12.5 Medical care and protection of participants**

In accordance with the Declaration of Helsinki, the informed consent document is drafted in a language and script that the participant or their legal representative/guardian can understand. It details the purpose, methods, and processes of the study, including treatment measures, grouping, testing, potential benefits, and risks, as well as alternative diagnostic and treatment options available. It also ensures that participants' personal data are confidential and that their participation is completely voluntary. Participants have the right to withdraw from the study at any stage without discrimination or retaliation, and their medical treatment and rights will not be affected. If any damage related to the clinical study occurs, participants will be entitled to appropriate compensation. Only after obtaining the signatures and dates from the participant and their legal representative/guardian can the clinical study

proceed. If the participant and their representative are illiterate, a witness must be present, and after a detailed explanation and oral consent, the witness must sign and date the consent form. Researchers must rigorously implement the informed consent process to ensure that participants fully understand the study requirements and cooperate with the research.

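### Section 12.3(11) lets the consent form be signed after the study has begun, with no latest time, which contradicts inclusion criterion 5 and section 12.5

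*Protocol*

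**What the plan says.** The protocol deals with the timing of the signature in three places.

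- Section 12.3, item (11), first sentence, gives the general rule: "The signing of the informed consent should occur before any research procedure" is carried out.
- The second sentence of the same item relaxes it: "If the consent cannot be signed before the study due to justifiable reasons, it should be signed as soon as possible". It also asks for a date and an explanation to be noted on the form. It does not say which reasons qualify or by when the signature must be obtained.
- Section 3.1.2 lists as inclusion criterion 5: "Signed the informed consent form".
- Section 12.5 states: "Only after obtaining the signatures and dates from the participant and their legal representative/guardian can the clinical study" proceed. No exception is given.

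Four other places fix the sequence of events around the signature.

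- Section 4.5: "Baseline assessments will be performed before enrollment".
- Section 2.3: "Participants will choose one of these envelopes after agreeing to the principle of random allocation". A signature is not mentioned there.
- Section 4.3: "Participants in both groups will receive a single treatment session, with a 10-minute auricular needle retention time".
- Section 5.4.1: "The primary outcome will be the change in pain intensity from baseline to 10 minutes after treatment", measured by VAS.

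**The concern.** A site that follows the second sentence of 12.3(11) can enter a patient whom 3.1.2(5) makes ineligible and whom 12.5 bars from proceeding. In most trials a short delay in signing would still leave the outcome far off. Here the needle stays in for 10 minutes and the primary reading is at 10 minutes, so even a modest delay could carry the signature past allocation and past the primary outcome.

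Two things are at stake. The first is eligibility: the protocol's own rules conflict on whether such a person belongs in the trial and on what follows. The second is that someone asked to sign after feeling the result could decline because of it. The protocol does not say how to treat a randomised person who never signs.

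**Working it through.** No figure in the plan depends on this point, so there is nothing to recompute. The check is a comparison of the rules against each possible time of signing.

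**Step 1. Order of events.** Baseline assessments come before enrollment (4.5). The envelope is chosen next (2.3), then comes the single session (4.3), with the primary VAS at 10 minutes (5.4.1). The protocol gives no interval between baseline and envelope, or between envelope and needle.

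**Step 2. Each possible time of signing against each rule.**

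| Form signed | 12.3(11), first sentence | 12.3(11), second sentence | 3.1.2(5) | 12.5 |
|---|---|---|---|---|
| Before baseline | met | not needed | met | met |
| After baseline, before envelope | breached, if baseline counts as a research procedure | allowed, if the study counts as begun | met by the time of allocation | depends on when the study is taken to begin |
| After envelope, before the 10-minute VAS | breached | allowed | failed at allocation | breached |
| After the 10-minute VAS | breached | allowed | failed at allocation | breached |

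Only the first row satisfies every rule beyond doubt. The exception sets no latest time, so it reaches the last two rows, and there it conflicts with 3.1.2(5), with 12.5 and with the sentence before it. The second row shows that a late signature need not follow allocation.

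**Step 3. What the protocol then does with the participant.** A person randomised unsigned does not meet criterion 5.

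- Section 3.1.4(1) says that wrongly included cases are to be excluded.
- Section 3.1.5(4) sends excluded and dropped cases to the intention-to-treat analysis.
- Section 11.1.1.1 defines the full analysis set as everyone randomised.

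So the person is excluded as a case but kept in the primary analysis set. As a general rule for eligibility errors this can be made to work. For someone who never signs, the protocol would be keeping data without a documented consent, and it does not address that case.

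**Step 4. Who would need the exception.**

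- Participants are outpatients (12.4) aged 18 to 60 (3.1.2).
- Those who cannot cooperate because of severe mental illness or intellectual disability are excluded (3.1.3(4)).
- Illiteracy is handled by a witness (12.3(10), 12.5) and legal incapacity by a representative (12.3(8)).

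The protocol names no group for which a deferred signature is required. Sections 9.3, 12.3(8) and 12.5 also ask for signatures from family or a representative. A relative who is not at the clinic is therefore a foreseeable reason for invoking the exception.

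**The case against.** The strongest reply is that the exception defers a signature, not consent itself. Section 2.3 still requires the participant to accept random allocation before choosing an envelope, and 12.3(7) requires that the information be understood before the person volunteers. Two sections without exceptions already bar unsigned entry, and nothing shows that deferred signing is a planned route into the trial. Participants may also withdraw at any stage (12.2, 12.3(3), 12.5), so loss that depends on the result is not peculiar to this clause.

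Most of this is fair, and it rules out several stronger readings that a reader might infer:

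- *That the clause means consent after allocation, and probably after the outcome.* The text supports only that this is permitted. Agreement to allocation comes first under 2.3, and no interval is stated that would make a signature after the outcome likely.
- *That a late signature cannot precede randomisation.* Baseline assessments come before enrollment, so a signature can be late under the first sentence of 12.3(11) and still precede the envelope.
- *That data from people who later decline to sign could not be used in the full analysis set.* No section says so. That set contains everyone randomised.
- *That the clause would materially bias the treatment comparison.* The protocol gives no frequency of late signing and no refusal rate, so any figure would rest on invented inputs.

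The reply does not remove the contradiction. Agreement under 2.3 concerns allocation and mentions no signature, so it satisfies neither 3.1.2(5) nor 12.5. That other sections bar unsigned entry is the reason the exception conflicts with them.

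**Conclusion.** The point holds as an internal contradiction of minor severity. The second sentence of 12.3(11) allows a signature after the study has begun, for undefined reasons and with no latest time. Criterion 5, section 12.5 and the first sentence of the same item do not. Because the session and the primary reading are so short, the exception permits a signature after allocation or after the primary outcome, but the documents do not say that this will happen. No numerical effect can be derived from the protocol and none is claimed. The conclusion rests on the wording alone, with one reading assumed: that criterion 5 must be met by the time of allocation, as an inclusion criterion ordinarily must.

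**What to change.** Delete the second sentence of 12.3(11), so that the item agrees with 3.1.2(5) and 12.5. Add to 2.3 that no envelope is chosen or opened until the consent form has been signed and dated. This closes the gap in 2.3, which at present ties envelope selection to agreement but not to a signature.

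The cost is one sentence removed and one added. A patient who cannot sign beforehand is not enrolled, but criterion 5 already requires that, so nobody eligible under the present criteria is lost. The sample size, the analysis sets and the analysis methods are unaffected.

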## **12.4 Source of participants**

All participants with ALS in this study will be recruited from the outpatient department of the Second Affiliated Hospital of Yunnan University of Chinese Medicine.

## **12.5 Medical care and protection of participants**

In accordance with the Declaration of Helsinki, the informed consent document is drafted in a language and script that the participant or their legal representative/guardian can understand. It details the purpose, methods, and processes of the study, including treatment measures, grouping, testing, potential benefits, and risks, as well as alternative diagnostic and treatment options available. It also ensures that participants' personal data are confidential and that their participation is completely voluntary. Participants have the right to withdraw from the study at any stage without discrimination or retaliation, and their medical treatment and rights will not be affected. If any damage related to the clinical study occurs, participants will be entitled to appropriate compensation. Only after obtaining the signatures and dates from the participant and their legal representative/guardian can the clinical study

proceed. If the participant and their representative are illiterate, a witness must be present, and after a detailed explanation and oral consent, the witness must sign and date the consent form. Researchers must rigorously implement the informed consent process to ensure that participants fully understand the study requirements and cooperate with the research.

## **13 Summary and data preservation**

Upon completion of the research project, a summary of the data will be made, and original materials such as the research protocol, informed consent forms, ethical committee approvals, ethical committee member list, completed and signed case report forms with dates, original serious adverse event reports, CRF forms, operation manuals, researcher's signature stamps, and all related original materials will be archived by the research team.
